# The protocol for the Be Our Ally Beat Smoking (BOABS) study, a randomised controlled trial of an intensive smoking cessation intervention in a remote Aboriginal Australian health care setting

**DOI:** 10.1186/1471-2458-12-232

**Published:** 2012-03-23

**Keywords:** Indigenous, Aboriginal, Torres Strait Islander, Randomised controlled trial, Smoking cessation, Study protocol, Be Our Ally Beat Smoking (BOABS) Study

## Abstract

**Background:**

Australian Aboriginal peoples and Torres Strait Islanders (Indigenous Australians) smoke at much higher rates than non-Indigenous people and smoking is an important contributor to increased disease, hospital admissions and deaths in Indigenous Australian populations. Smoking cessation programs in Australia have not had the same impact on Indigenous smokers as on non-Indigenous smokers. This paper describes the protocol for a study that aims to test the efficacy of a locally-tailored, intensive, multidimensional smoking cessation program.

**Methods/Design:**

This study is a parallel, randomised, controlled trial. Participants are Aboriginal and Torres Strait Islander smokers aged 16 years and over, who are randomly allocated to a 'control' or 'intervention' group in a 2:1 ratio. Those assigned to the 'intervention' group receive smoking cessation counselling at face-to-face visits, weekly for the first four weeks, monthly to six months and two monthly to 12 months. They are also encouraged to attend a monthly smoking cessation support group. The 'control' group receive 'usual care' (i.e. they do not receive the smoking cessation program). Aboriginal researchers deliver the intervention, the goal of which is to help Aboriginal peoples and Torres Strait Islanders quit smoking. Data collection occurs at baseline (when they enrol) and at six and 12 months after enrolling. The primary outcome is self-reported smoking cessation with urinary cotinine confirmation at 12 months.

**Discussion:**

Stopping smoking has been described as the single most important individual change Aboriginal and Torres Strait Islander smokers could make to improve their health. Smoking cessation programs are a major priority in Aboriginal and Torres Strait Islander health and evidence for effective approaches is essential for policy development and resourcing. A range of strategies have been used to encourage Aboriginal peoples and Torres Strait Islanders to quit smoking however there have been few good quality studies that show what approaches work best. More evidence of strategies that could work more widely in Indigenous primary health care settings is needed if effective policy is to be developed and implemented. Our project will make an important contribution in this area.

**Trial Registration:**

Australian New Zealand Clinical Trials Registry (ACTRN12608000604303)

## Background

While Australian Aboriginal peoples and Torres Strait Islanders (Indigenous Australians) historically had access to nicotine containing plants growing naturally, heavy use was presumably rare. However the addictive nature of nicotine was readily exploited by Europeans [1], with tobacco being supplied as part of rations on cattle stations and missions until the 1960s [2]. Tobacco smoking is now normalised in Indigenous Australian society [1]. In 2007, the prevalence of smoking in the non-Indigenous population was 19% [3]. In the 2004 National Aboriginal and Torres Strait Islander Health Survey, 52% of Indigenous Australians reported being smokers [4]. In contrast, the 2007 National Drug Strategy Household Survey reported that 34% of Indigenous Australians were smokers [3] whereas the current prevalence is estimated to be in excess of 45% [5]. Over 35% of Indigenous Australian people aged between 12 and 17 report regular smoking and smoking prevalence increases with age [6,7]. This early regular tobacco consumption can lead to increased dependence upon nicotine and reduces the success of cessation attempts later in life [8]. A number of reports indicate that Indigenous Australians are less likely to stop smoking compared with non-Indigenous people [9].

Smoking among Aboriginal peoples and Torres Strait Islanders contributes significantly to higher rates of hospitalisation and death from tobacco-related conditions and poorer self-reported health [10-12]. Much of the health disparity between Indigenous and non-Indigenous people in Australian is attributable to conditions that are either due to or made worse by tobacco consumption. Smoking substantially increases the risk of both macrovascular and microvascular complications of diabetes and may have a role in the development of type 2 diabetes [10]. Indigenous health professionals are reported to be more likely to smoke than non-Indigenous health professionals and to have lower rates of awareness about the detrimental effects of smoking behaviour [13].

Helping established tobacco smokers to stop smoking and maintain this is notoriously difficult in any setting. Interventions to help smokers to quit have, even in the controlled setting of experimental randomised controlled trials (RCTs), a success rate of at most 25% at 12 months and are more typically substantially lower. The quit rates in primary health care settings, particularly when health workers approach clients to quit, are likely to be lower than in settings where clients have specifically sought help [2]. Motivation to quit prior to being involved in an intervention did not predict success in quitting [14,15]. Several RCTs have demonstrated that 5-22% of participants who were not interested in quitting at the start of their participation had quit smoking at the follow-up (reviewed in [16]). The data from these studies suggest that quitting can occur among those who appear to be relatively unmotivated smokers and can be encouraged by intervention and the use of pharmacotherapy (e.g. nicotine replacement therapy (NRT)).

Helping Aboriginal peoples and Torres Strait Islanders to quit smoking is complex, due in part to the multiple life stressors experienced by them [17], and the need to identify and support local champions [18]. Integrated services provided by Aboriginal Community Controlled Health Services (ACCHS), which provide a 'culturally safe' environment have been shown to be successful, and interventions can reduce risk [19].

Given the stark and persisting health inequalities borne by Indigenous Australians [20] - despite existing evidence-based interventions - it is imperative research is undertaken in this setting to provide insights into how best to respond to primary and secondary disease prevention. RCTs provide high-quality research and evidence, and can be undertaken in this setting. In 2002 Kimberley ACCHS took part in a double blind, multi-centre, RCT that was conducted by the National Aboriginal Community Controlled Health Organisation (NACCHO Ear Health Trial) [21]. The research methodology of this RCT placed Aboriginal people in control of their own research [22]. RCTs when carried out in ACCHS need to be simple, modified to the local setting, and embedded in primary health care for them to be successful and sustainable.

This study aims to test the efficacy of a culturally appropriate multidimensional intensive smoking cessation intervention provided by Aboriginal researchers in helping Aboriginal peoples and Torres Strait Islanders to become non-smokers.

### Hypothesis

A culturally appropriate, multidimensional, intensive smoking cessation intervention, provided by trained Aboriginal researchers, will be more effective than current standard practice in achieving and sustaining cessation to tobacco consumption among Aboriginal peoples and Torres Strait Islanders.

## Methods/Design

### Objectives

The primary objectives of this study are to 1) develop a locally-tailored, intensive, multidimensional smoking cessation program utilising identified Aboriginal smoking prevention officers, and 2) to determine the effectiveness of this program through implementation of a RCT comparing it with a standard primary care based brief intervention strategy in two Kimberley ACCHS. Secondary objectives include encouraging research interest and capacity among Aboriginal health staff and to build skills in Good Clinical Practice as they relate to the conduct and evaluation of a RCT. The Aboriginal researchers employed on the study named it the BOABS (Be Our Ally, Beat Smoking) Study.

### Study design

This study is a parallel, randomised controlled study. Participants are randomly allocated to one of two study arms: the 'intervention' group who participates in the BOABS program over 12 months, or the control group who are allocated to 'usual care' (i.e. they do not participate in the BOABS program). Aboriginal researchers are trained to deliver the BOABS program, the goal of which is to help Aboriginal people quit smoking. Data collection occurs at baseline (when participants enrol in the study), and at six and 12 months following enrolment. The primary outcome of interest is the proportion of subjects who self-report smoking cessation with urinary cotinine validation at 12 months. Figure 1 outlines the flow of participants through the study.

**Figure 1 F1:**
[figure not shown]
**Flowchart for a randomised controlled trial of a culturally appropriate, multidimensional, intensive smoking cessation intervention provided by trained Aboriginal researchers**.

### Study populations

This study is being conducted in Derby and Kununurra in the remote Kimberley region of far north Western Australia (see Figure 2). The Kimberley is one of the most isolated and sparsely populated areas of Australia with a resident population of 29,298 [23] spread over 423,517 km^2^. While Indigenous Australian people are socioeconomically disadvantaged everywhere in Australia [24], remote Indigenous people, including most residents of the Kimberley and the adjacent Northern Territory (NT), are in the lowest socioeconomic quartile of Indigenous people [24,25], the most disadvantaged group within the most disadvantaged population in Australia. The target population for this study are Aboriginal and Torres Strait Islander smokers who resided in or near these two towns. The sampling unit is Aboriginal and Torres Strait Islander smokers (aged 16 years and over).

**Figure 2 F2:**
[figure not shown]
**Sites where the Be Our Ally Beat Smoking (BOABS) Study is being conducted, the Kimberley, Western Australia**.

The Kimberley region extends 1100 km from east to west and 850 km from north to south. The study sites are Derby Aboriginal Health Service in Derby and Ord Valley Aboriginal Health Service in Kununurra. The centralised coordinating site is the Kimberley Aboriginal Medical Services Council in Broome

### Inclusion criteria

Participation in the trial is based on the following inclusion criteria:

• Aboriginal and/or Torres Strait Islander

• ≥ 16 years of age

• Self-reported current smoker or quit within 2 weeks of recruitment

• Thinking about cutting down or quitting smoking

• A regular client of Derby Aboriginal Health Service (DAHS) in Derby or Ord Valley Aboriginal Health Service (OVAHS) in Kununurra

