### Outcome measures

Primary endpoint:

• The proportion of participants who were not smoking tobacco at 12 months as determined by self-report and urinary cotinine level consistent with no recent tobacco consumption [26].

Secondary endpoints:

• The proportion of participants who were not smoking at 6 months as determined by self-report.

• The proportion of participants reporting excellent or very good health using a self-reported health questionnaire [27].

• The proportion of participants who reported 20% or greater reduction in the number of cigarettes smoked each week.

• Process evaluation indicators: a mix of quantitative and qualitative measures to assess how well the intervention program was implemented according to the protocol e.g. number of 'face-to-face' meetings completed, challenges and solutions in delivering the program.

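### Recent quitters are eligible although the population is described as smokers; entry smoking status should be recorded, adjusted for, and used for a pre-specified analysis of those smoking at entry

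*Protocol article*

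**What the plan says.** Under Inclusion criteria, the smoking criterion has two limbs: "Self-reported current smoker or quit within 2 weeks of recruitment". The next item on the same list is "Thinking about cutting down or quitting smoking". Under Study populations, the description has one limb: "The target population for this study are Aboriginal and Torres Strait Islander smokers"; the sampling unit is also given as smokers, and the abstract describes participants in the same way.

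The primary endpoint, under Outcome measures, is "The proportion of participants who were not smoking tobacco at 12 months as determined by self-report and urinary cotinine level" in the non-smoking range. It sets no condition on smoking status at entry, and neither does the six-month self-report endpoint. A further secondary endpoint is a fall of at least 20% in weekly cigarettes.

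The Background states the aim as testing the intervention "in helping Aboriginal peoples and Torres Strait Islanders to become non-smokers". The Hypothesis is wider: the program "will be more effective than current standard practice in achieving and sustaining cessation to tobacco consumption". The sample-size section speaks of maintaining cessation, and the counselling content includes dealing with relapse.

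Baseline characteristics names the adjustment variables: sex, age, education, marital status, and the smoking status of the partner and household. The participant's own status at entry is not named, although the list is introduced as examples. Randomisation is by site only. Eligibility is confirmed and the first questionnaire completed before allocation.

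**The concern.** A participant who has already stopped faces a different task from one who is still smoking. The first needs to stay stopped; the second needs to stop and then stay stopped. The hypothesis names both tasks, but the protocol describes only comparisons that pool them. A reader who has been told that the trial enrols smokers will take the pooled quit rates as the answer to whether the program gets smokers to quit, and those rates may not show that.

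The matter is worth settling because events are few: the planned rates imply about 23 quitters in the whole trial. Entry status is also plausibly one of the strongest predictors of 12-month status, yet the named adjusters cover other people's smoking and not the participant's own.

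Two smaller mismatches follow from the same criterion. Someone who has already quit fits poorly with being required to be thinking about cutting down or quitting. And a person whose baseline count is zero cannot reduce it by 20%, so would be a built-in failure on that endpoint.

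**Working it through.** **Inputs from the protocol (Sample size).** Two-sided alpha 0.05; power 0.80; one intervention participant to two controls; 12-month rates 3% (control) and 13% (intervention); 106/212 before loss and 120/240 after allowing for loss.

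**Inputs assumed (not in the protocol).** Share of recent quitters f = 2% to 20%; their 12-month abstinence in the control arm q = 10% to 30%, central value 20%; program effect in them either zero or +10 points. The 3% and 13% are taken as the rates in those smoking at entry.

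**The plan's own figure.** With k = 2 and d = 0.10, n = [1.96·√(p̄(1−p̄)(1+1/k)) + 0.8416·√(p₁(1−p₁)+p₂(1−p₂)/k)]² / d², followed by the continuity correction (n/4)·[1+√(1+2(1+1/k)/(nd))]². With the weighted mean p̄ = (0.13 + 2×0.03)/3 = 0.0633, this gives 79, or 93 corrected. With the unweighted mean p̄ = 0.08, it gives 90.6, or 105.1 corrected, hence 106/212. The stated size is therefore reproducible under a conservative variant. By the usual weighted formula without correction, power is 0.89 at 106/212 and 0.92 at 120/240. This is a side check; the point does not depend on it.

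**Expected quitters as planned.** 0.13×120 + 0.03×240 = 15.6 + 7.2 = 22.8.

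**Adding recent quitters.** Pooled rate = (1−f)·p + f·q, with p = 0.03 or 0.13. Recent-quitter events = 360·f·q. Power = Φ[(d − 1.96·SE₀)/SE₁], with d now the pooled difference, SE₀ from the weighted pooled rate and SE₁ from the separate rates.

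Worked case, f = 10%, q = 20%, no effect in recent quitters:
- control: 0.9×0.03 + 0.1×0.20 = 4.7%; intervention: 0.9×0.13 + 0.1×0.20 = 13.7%; difference 9.0 points
- all quitters: 240×0.047 + 120×0.137 = 11.28 + 16.44 = 27.7
- from recent quitters: 360×0.10×0.20 = 7.2, or 26% of all; in controls 0.020/0.047 = 43%
- power at 120/240: SE₀ = 0.0298, SE₁ = 0.0342, (0.090 − 1.96×0.0298)/0.0342 = 0.92, so 0.82

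| Share f (q = 20%) | Rates, no effect in recent quitters | Share of all quitters | Share of control quitters | Power 120/240 (106/212) | Power 120/240 with +10 points in recent quitters |
|---|---|---|---|---|---|
| 5% | 3.9% v 13.4% | 14% | 26% | 0.88 (0.84) | 0.90 |
| 10% | 4.7% v 13.7% | 26% | 43% | 0.82 (0.78) | 0.88 |
| 20% | 6.4% v 14.4% | 44% | 62.5% | 0.68 (0.63) | 0.83 |

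**Sensitivity to q.** At f = 10% with no effect in recent quitters, power at 120/240 is 0.86, 0.82 and 0.79 for q = 10%, 20% and 30%. At f = 2%, it is at least 0.90 for every q in the range.

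**Size of the supporting analysis.** At f = 10%, those smoking at entry number 108 and 216, with 0.13×108 + 0.03×216 = 20.5 expected quitters. The same power formula at 13% v 3% gives 0.90.

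**The case against.** The strongest reply is that the mixture is what the protocol set out to test. The hypothesis names sustaining cessation, the sample-size section speaks of maintaining it, and the counselling covers relapse. Someone a few days into a quit attempt is a natural participant. This stands, and it rules out two readings that a reader might be tempted by: that the endpoint is invalid, and that recent quitters should be excluded. A reader might also infer bias. The documents do not support that: status is fixed before allocation, so recent quitters are balanced in expectation and the type I error rate is unaffected. Nor must a recent quitter stay continuously abstinent to count; the endpoint is status at 12 months, so relapsing and quitting again also succeeds.

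The dilution figures rest on undocumented inputs, and this also stands. Loss of effect arises only if the program does less for recent quitters than for smokers. With an equal 10-point effect, the difference stays at 10 points and power slips only because the base rates are higher. If the planned 3% already describes the whole enrolled control group, the 20% share cannot occur with 20% abstinence, since recent quitters alone would supply 4%. The protocol also hints at a small share: few people met the former readiness criterion, and the clinic route approaches current smokers. Community recruitment is not limited in that way, so the hint does not settle the matter.

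Finally, the covariate list is illustrative, and a full analysis plan may add to it. That is fair, and it is why no claim is made that adjustment for entry status is ruled out. It does not remove the mismatch between the eligibility criteria and the population description, or the reduction endpoint that recent quitters cannot meet.

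**Conclusion.** The point holds as an inexpensive improvement to the plan and not as a flaw in the primary comparison. The protocol contradicts itself on who is enrolled, and the analyses it describes do not separate getting smokers to quit from keeping recent quitters abstinent.

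The size is uncertain. On the central assumption (20% abstinence in both arms, no program effect in recent quitters), a 10% share cuts the expected difference from 10 to 9 points and the risk ratio from 4.3 to 2.9. Power stays above 0.80 at full recruitment and falls just below it at 106/212. A 20% share would be serious; a share of a few per cent would hardly matter. Neither the share nor the effect in recent quitters is documented, so no single figure should be taken as the expected loss. A claim that the trial is underpowered for this reason would go beyond the protocol.

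**What to change.** 1. Reconcile the abstract and Study populations with the Inclusion criteria by stating that people who quit within two weeks of recruitment are included, and word the cutting-down-or-quitting criterion so that it can apply to them.
2. Record entry status as a two-level baseline item (smoking, or already quit within two weeks), before allocation.
3. Name that item among the variables in the adjusted analysis.
4. Keep the all-randomised analysis as primary, and pre-specify the 12-month cotinine-confirmed endpoint among those smoking at entry as a supporting analysis. Because the group is defined before randomisation, it remains a randomised comparison. Say that it supports the interpretation and does not replace the primary result if the two differ.
5. Evaluate the 20% cigarette-reduction endpoint in those smoking at entry.

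The cost is one baseline item, some wording and one table. The protocol does not say that the two limbs of the eligibility criterion are recorded separately, so the item may need to be added to the form. The statistical price is one more model term with only about 23 expected events, and somewhat fewer participants in the supporting analysis. The staff are not blinded to allocation, so these choices should be fixed before outcome data are examined.

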### Exclusion criteria

People are excluded from participation in the trial based on the following criteria:

• Unable to provide informed consent

• A health condition that would prevent them from completing the trial

• Unlikely to be available for follow up at 12 months

### Randomisation: allocation, concealment and sequence generation

Block randomisation (36 participants per block × 6 blocks) is used to randomly assign participants to Group 1 (control group) or Group 2 (intervention group). Each site has 216 envelopes allocated. Each block has 24 participants randomly assigned to Group 1 and 12 to Group 2 using a computer generated random list of dichotomous outcomes (control or intervention) generated for each site using Excel 2007 software (Microsoft, Redmond, WA, USA). While only 5 blocks are required an extra block is generated to allow for contingencies that might require extra participants to be recruited. Envelopes are filled and sealed by an individual who is not involved with the study or its analysis. Envelopes are kept off-site and under the supervision of administrative staff based at a centralised coordinating site (the Kimberley Aboriginal Medical Services Council in Broome). Allocation occurs via telephone with envelopes being opened in sequential order for each site only once a participant is consented and enrolled in the study, eligibility is confirmed, an identification number is, assigned and the first questionnaire completed.

### Blinding

Due to the nature of the intervention and the 2:1 weighting of participants in the control and intervention arms, the participants, research team and local healthcare staff know whether each participant belongs to the control or intervention group. The staff performing the urinary cotinine assay are unaware of the allocation.

### Proposed intervention

Participants are told that they will be randomly assigned to a group that receives 'usual care', or a group that receives extra support visits by an Aboriginal smoking cessation officer, and that a questionnaire will be administered when they enrol, and at six and 12 months following enrolment.

#### Participants assigned to the control group

Participants allocated to the control group receive the usual practice of the service, including but not limited to advice from clinical staff regarding the harmful effects of smoking, advice regarding quitting, pharmacotherpay, self-initiated follow up, and access to usual services offered by the service (e.g. at DAHS clients are offered participation in lifestyle and primary prevention education classes).

